#### Randomization

The two randomization sequences (i.e., sex stratification) are generated with a 1:1 ratio (i.e., intervention versus Education Control condition) using a computerized random permuted block sequence generator (Random Allocation Software [60]) with concealed block sizes to ensure study staff blinding. A sequential, double envelope system is utilized to conceal individual placement. The sequential envelopes are labeled and colour-coded according to sex. The delegated study staff complete randomization by selecting the next sequential envelope per applicable stratification, affix the sticker that reveals the condition placement on the participant’s source document and enter the group placement information into IRIS. The next study steps released by IRIS are dependent on the group placement entered; IRIS unlocks the appropriate user interface (i.e., Strongest Families Smart Website intervention with weekly telephone coaching-Intervention condition; Static website with parenting tips-Education Control condition). After randomization, the participants receive an email informing them of the randomization results and a link to the relevant website. In addition, the participants are not restricted from seeking other assistance for problems that they encounter.

### Interventions

#### Risk management

This is a minimal risk trial. Staff are trained in risk management reporting protocols to identify and report any suspicion of abuse and neglect according to the local legal requirements.

#### Website security

The internet traffic between the participant and the website is protected by a HyperText Transfer Protocol Secure (HTTPS) communications protocol. The website is hosted on a secure server maintained by the University of Turku IT Services in Finland.

#### Education control condition

The participants randomized to the Education Control condition receive access to a static website with parenting tips as well as a single 45-minute telephone call with a coach reviewing the parenting tips. The Education Control was chosen as the Control condition as opposed to a waitlist control or standard care for the following reasons: (1) a waitlist control condition does not allow for a long-term follow-up, (2) for the majority of families in the Finnish population, standard care constitutes no care at all, and (3) the Education control was deemed as an ethical alternative for parents with a challenging child.

#### Intervention condition

The participants randomized to the Intervention condition receive a Smart Internet version of the Strongest Families telephone-based program [38,61,62], an 11-session, evidence-based parenting program, that focuses on skills for strengthening parent–child relationships; reinforcing positive behaviour; reducing conflict; managing daily transitions; planning for potentially problematic situations; and promoting pro-social behaviour. The Strongest Families telephone-based program was initially designed to target 3–12 year-old children. For the current study, the program content was modified into a web-based format and in accordance with the developmental level of 4 year-old children. Minor culturally appropriate changes were made throughout the program to accommodate for issues such as differences in the schooling and daycare systems between Finland and Canada.

The participating parents are asked to complete the 11 Strongest Families sessions online. The participants are encouraged to complete one session per week and at times most suitable to their daily life using a computer with an internet connection. Only one parent is the active participant during the program; however, the participant is encouraged to share the program content with the other partner when possible. The child does not take part in the telephone calls or use the website. The participant works through the online material for each session including exercises, instructional videos and skill demonstration audio and video clips. During the sessions, the participants are required to complete specific knowledge-based and experience-related questions. The participants are encouraged to complete each session in approximately one week after which the session concludes with a weekly telephone call with a trained coach (with health care professional certification) who provides support, responds to participants’ questions and reviews successful implementation of the program skills. If session skill adoption is considered adequate based on the coach’s professional experience, the next session is introduced at the end of the telephone call. Otherwise, the participant is encouraged to spend additional time with session content to acquire a necessary skill level.

#### Description of strongest families components

The Strongest Families Smart Website intervention has four components. First, the parenting skills curriculum is based on our Strongest Families telephone-based program, an approach derived from programs developed by members of this team [36,37]. There are also two booster sessions to encourage maintenance of skills and outcome gain (i.e., 2–3 months and 4–5 months after intervention). Second, it is a personalized website that tracks and uses activities and interactions to modify the intervention. Each participant’s interactions with the website are personalized by using such factors as the child’s name, child’s problems and strengths, and preferred activities. Each weekly session’s examples and homework tryout pages are populated with the personalized content [63]. The participants are reminded of upcoming appointments or prompted if they had visited the website infrequently. Third, during the initial 11-week phase and booster sessions, the participants are assisted and monitored on their progress by a coach. The coach contacts the participant each week by telephone (45-minute call), reviews their progress, introduces new skills, facilitates the solution of problems, and provides support and encouragement. Prior to each session, the coach reviews the participant’s use of the website and any automatic messages sent to the participants.

#### Treatment fidelity

In order to ensure treatment fidelity, a number of steps are followed, including the recording of telephone calls, strict adherence to standard study protocol procedures, cultural adaptation of the program material to Finnish, and training with coaches. Finnish coaches are health care professionals or semi-professionals with a background in children’s services. They are trained by an experienced Strongest Families clinician to ensure proper application of the program in Finland. Specifically, in addition to ongoing coaches’ meetings to discuss cases conducted initially every two weeks and then once a month with the Canadian team, three training and question/answer sessions for the Finnish group are conducted to ensure correct administration of the Strongest Families Smart Website intervention: (1) one week of intensive program content review, (2) one week of revised curriculum and research protocol training and regulation review per Good Clinical Practice according to the ICH guidelines, and (3) a final process review after the RCT had begun. The Finland study team has weekly study meetings, and coach supervision meetings are held weekly both individually as well as with all of the coaches to review and discuss the cases. All of the telephone calls are recorded and a portion are audited by the Finland coach supervisor and scored for competency evaluation. If scores do not reach competency, additional training is completed with the coach using additional telephone call evaluations.

#### Trial status

Recruitment for the RCT is currently underway, with 337 participants on August 27^th^, 2013. The Strongest Families Smart Website-Finland was launched in January, 2012. We aim to recruit a sample of 500 families and to complete the one year follow-up in 2015 (see Figure 1 for SFFC Smart Website Intervention Consort Flow Diagram).

**Figure 1 F1:**
[figure not shown]
**SFFC Smart Website Intervention Consort Flow Diagram.** (Flow Diagram of the progress through the phases of the SFFC RCT [i.e., enrollment, intervention allocation, baseline, and follow-up]).

### Measures

The child and parent applicable measures are completed online using secured access to the Strongest Families Smart Website intervention. The teachers are asked to complete the SDQ and TRF on paper and submit the completed questionnaires to the study team. With the exception of the screening measure, all post-screening measures are administered at baseline, at 6 months and at 12 month follow-up.

#### Screening measure

Screening for the RCT is conducted using the *Strengths and Difficulties Questionnaire* (SDQ) [56]. The SDQ is a brief behavioural screening questionnaire for use with 3–16 year-old children and adolescents. The measure is composed of 25 items that are divided between 5 scales: (1) emotional symptoms, (2) conduct problems, (3) hyperactivity/inattention, (4) peer relationship problems, and (5) prosocial behaviour. Research has found that the SDQ displayed adequate validity in Finnish samples of school-aged children and adolescents, with one study of Finnish school-aged children and adolescents reporting inter-rater agreement for total scores on the parent, teacher, and self-report measures of 0.38-0.44 and internal consistency of 0.71 [64,65]. Another study of Finnish adolescents found correlations between the items and their respective subscales ranging from moderate to high (r = 0.47–0.73), and subscale internal consistency ranging from alpha = 0.53–0.71 [66]. The conduct problem scale of the SDQ is used for screening purposes. Recent research with the parent-rated SDQ in preschool children found that the measure has internal consistency of alpha = 0.58 for the conduct problems scale and acceptable concurrent validity [67].

#### Demographics

Background information on participant native language, marital and socioeconomic status (SES), parental education, and child developmental and medical history is collected.

#### Primary outcome measure

The *Externalizing subscale of the Child Behavior Checklist-Parent Report Form (CBCL) for ages 1½-5* of the Achenbach System of Empirically Based Assessment (ASEBA) [52], the most widely employed, validated and age-normed measure of disruptive behaviour [68-74], is used as the primary outcome measure. The Externalizing subscale of the CBCL consists of 34-items that measure both the angry, irritable, defiant, uncooperative behaviour associated with ODD as well as a broader range of closely related externalizing problems [52]. The CBCL has good test-retest reliability (e.g., 0.81) and criterion validity (e.g., 0.56-0.87) [52].

#### Secondary outcome measures

##### Parenting skills

*The Parenting Scale (PS)*[53,54] is used to measure parenting skills. The PS is a 30-item parent/caregiver report for children ages 1–12 years. It measures parenting and discipline styles, particularly those that are found to be related to the development and/or maintenance of child disruptive behaviour problems. The PS has adequate internal consistency (e.g., 0.84) and convergent validity (e.g., 0.53) [54].

##### Parent conflict

The *Parent Problem Checklist (PPC)* is a 16-item scale measuring parental conflict. Interparental conflict is recognized as a risk factor for many childhood behavioural and emotional problems. This scale has good reliability and validity. High scores on the PPC have been associated with parental reports of increased child problems, general conflict, and lower marital satisfaction [75].

##### Parent’s sense of coherence

The *Sense of Coherence Scale (SOC-13)* is used to assess parents’ sense of coherence (i.e., a global view of the world and individual environment as comprehensible, manageable, and meaningful) [76,77]. The SOC-13 consists of 13 questions with two anchoring phrases. The questions are rated between 1 and 7 on a Likert-type scale, with five items reverse-scored. The sum of all items yields a score from 13 to 91. The reliability and validity of the scale have been established in many studies, and the score of the SOC-13 has been found to correlate positively with various aspects of health and well-being, and negatively with perceived stressors and poor coping skills [76,78]. A systematic review examining 127 studies using SOC-13 found Cronbach alphas ranging from 0.70 to 0.92 and means ranging from 35.39 (SD 0.10) to 77.60 (SD 13.80) points [77].

##### Parental distress

The *Depression Anxiety and Stress Scale Short Form (DASS-21)*[55] is used to measure parental distress. It consists of three subscales (i.e., depression, anxiety and stress) combined into a measure of general distress [79]. The DASS-21 demonstrates strong internal consistency (e.g., 0.93 for the total scale) and adequate construct validity (e.g., 0.69 for the total scale) [80] and is sensitive to the effects of parenting interventions [81-83].

##### Child’s callous and unemotional traits

The *Inventory of Callous-Unemotional Traits (ICU)* is a 24-item questionnaire designed to provide a comprehensive assessment of traits that have been proven to be important for designating a distinct subgroup of antisocial and aggressive youth. The ICU has acceptable internal consistency (e.g., 0.77) and convergent validity (e.g., 0.19-0.44) [84,85].

#### Moderator measure

##### Parent attention-deficit/hyperactivity symptoms

The *Barkley Adult ADHD Rating Scale–IV (BAARS-IV-Quick Screen)*[86] is used to determine whether adult attention-deficit/hyperactivity disorder (ADHD) symptoms moderate the response of parents to the intervention [87]. This 14-item measure takes 3–5 minutes to administer and is linked to DSM-IV diagnostic criteria. It is a reliable and valid measure of current and childhood ADHD symptoms [86].

##### Program utilization measure

Each participant’s time on the website is downloaded using appropriate time-out values and the percentage of primary screens the participants observed. Program satisfaction and therapeutic alliance questions are released at the end of treatment for the intervention group only. Program satisfaction is also measured at 12 months.

##### Quality assurance

All aspects of the trial (e.g., data collection, telephone calls to the participants) are monitored to ensure that data is valid. Staff are centralized in a small call centre and carefully supervised to ensure the system’s integrity.

### Data management and analysis

#### Statistical analyses

Latent growth analysis, mixed effects regression, structured covariance analysis, or hierarchical linear modeling (HLM) will be used. The primary analysis will model the pattern of differences between the groups using growth curve analysis and the statistical software MLwinN [88]. With the primary outcome of CBCL externalizing scores, the analysis will treat repeated measures within individuals as Level 1, and differences in the coefficients between the Strongest Families Smart Website intervention and Education Control conditions as Level 2. In effect, the approach will be to estimate parameters of growth (i.e., the slope of the outcome scores over time) for each individual, and compare these between the Strongest Families Smart Website intervention and Education Control conditions. In addition to comparing trajectories of response among children allocated to the two arms of the trial, net differences in response will be estimated by transposing the intercept to the end of the trial [89]. This will allow a formal test of outcome differences. In addition, aggregate anonymous analysis of the characteristics of eligible children whose families did not consent to participate in the trial will be conducted. This will be important in understanding to whom the results of the trial can be generalized. The next step will be to test the possible moderating influence of program utilization using tracking reports of website activities (e.g., time on task, number of screens viewed, sessions completed).

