## Discussion

Disruptive behaviour disorders, such as ODD, are among the most costly of early childhood psychiatric disorders. We expect to have an efficient method to improve access to parenting services that are conveniently delivered to families in the comfort and privacy of their home, removing typical access barriers [39,45-50]. The intervention builds on earlier RCTs, as well as the knowledge of decision makers and parents about what will work in the real world environment. The Strongest Families Smart Website intervention developed through the SFFC program was designed to reduce the prevalence of child disruptive behaviour symptoms through early detection and accessible treatment using this innovative web-based delivery system. Our consumer preference studies [49,50,61,90-92] and our experience with Strongest Families [92] show that personalized coaching is critical to the success of the program.

We are conducting a population-based RCT study of 4 year-olds exhibiting elevated levels of ODD to examine a preventative intervention in the real world rather than in a more controlled situation. The information collected from this study will provide a detailed understanding of how the Strongest Families Smart Website intervention functions, how it can be improved, translated and disseminated. It is anticipated that these results will inform subsequent investigations, public policy, and the treatment of childhood disruptive behaviour problems.

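### The two-level primary model leaves no room for coach effects in the intervention arm, so its standard error is too small if outcomes vary by coach

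*Protocol article*

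**What the plan says.** **Model.** The Statistical analyses section of the protocol article first lists several candidate model families and then describes the primary analysis of the CBCL externalizing score: "the analysis will treat repeated measures within individuals as Level 1, and differences in the coefficients between the Strongest Families Smart Website intervention" and control conditions are Level 2. Growth parameters are estimated "for each individual, and compare these between the Strongest Families Smart Website intervention and Education Control conditions". That section names no coach level, coach random effect or cluster-robust standard error.

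**Intervention arm.** Under Description of strongest families components: "The coach contacts the participant each week by telephone (45-minute call), reviews their progress, introduces new skills". This runs through the 11-week phase, and a coach also assists in the two booster sessions. Under Intervention condition, the pace depends on the coach: "If session skill adoption is considered adequate based on the coach’s professional experience, the next session is introduced"; otherwise the family stays longer on the same material. The Discussion says that consumer preference studies and programme experience "show that personalized coaching is critical to the success of the program".

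**Control arm.** Under Education control condition, families receive a static website "as well as a single 45-minute telephone call with a coach reviewing the parenting tips".

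**Coaching team.** The number of coaches is not stated. Quality assurance says only: "Staff are centralized in a small call centre". Treatment fidelity describes common training, weekly supervision, recording of all calls, competency scoring of a portion, and retraining where scores fall short.

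**The concern.** Families are randomised individually, but after randomisation the intervention families are grouped by coach. The coach teaches the skills, helps solve problems and controls the pace, so coaches who differ in skill or style could shift the outcomes of all their families together. Individual randomisation does not remove a correlation that arises later through a shared coach. In the control arm the exposure to a coach is one call, so any such grouping is much weaker there. This is a partially nested design.

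A model whose only levels are occasion and individual sets the coach variance to zero. If that variance is positive, the model counts 175 intervention completers as 175 independent pieces of information when there are fewer. The confidence interval for the arm difference is then too narrow, the type I error exceeds 5%, and the real power is below what was planned.

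**Working it through.** **Inputs from the protocol article**
- Sample size section: 250 per group, 30% attrition, effect 0.30 to 0.35 SD, alpha 0.05.
- Design of the study: individual 1:1 allocation.

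**Inputs assumed, because the article does not give them**
- Power 80% and a two-sided test.
- Number of coaches k: 6, 10 or 20.
- Coach ICC (share of outcome variance in the intervention arm that lies between coaches): 0.01, 0.02 or 0.05.
- Equal caseloads, and no coach clustering in the control arm.

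**Step 1: reproduce the planned size.** For a plain two-sample comparison of means, n per arm = 2 × [(1.960 + 0.842)/0.30]² = 174.4, so 175 completers. Allowing for attrition, 175/0.70 = 250, the stated figure. Under these assumptions the planned size equals a calculation for independent families and contains no allowance for coaches. (At d = 0.35 and 90% power the same formula gives 172 completers and 246 enrolled, also close and also without such an allowance.)

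**Step 2: variance with clustering in one arm.**
- Families per coach: m = 175/k.
- Design effect in the intervention arm: DE = 1 + (m − 1) × ICC.
- Variance inflation of the arm difference: V = (1 + DE)/2.
- True two-sided error at nominal 5%: 2 × [1 − Φ(1.96/√V)].
- Power at d = 0.30 with the correct standard error: Φ(0.30/(√V × √(2/175)) − 1.96).

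Example, 10 coaches and ICC 0.05: m = 17.5; DE = 1 + 16.5 × 0.05 = 1.825; V = 2.825/2 = 1.4125; √V = 1.19; true error 2 × [1 − Φ(1.649)] = 9.9%; power 66%.

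**Step 3: the range.**

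| Coaches (assumed) | ICC (assumed) | Variance inflation | Correct SE / planned SE | True type I error | Power at d = 0.30 |
|---|---|---|---|---|---|
| any | 0 | 0% | 1.00 | 5.0% | 80% |
| 20 | 0.01 | 4% | 1.02 | 5.5% | 79% |
| 20 | 0.02 | 8% | 1.04 | 5.9% | 77% |
| 20 | 0.05 | 19% | 1.09 | 7.3% | 73% |
| 10 | 0.01 | 8% | 1.04 | 6.0% | 77% |
| 10 | 0.02 | 17% | 1.08 | 6.9% | 74% |
| 10 | 0.05 | 41% | 1.19 | 9.9% | 66% |
| 6 | 0.01 | 14% | 1.07 | 6.7% | 75% |
| 6 | 0.02 | 28% | 1.13 | 8.3% | 70% |
| 6 | 0.05 | 70% | 1.31 | 13.3% | 58% |

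These are normal approximations for a single end-of-trial difference.

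**The case against.** **A positive ICC is not shown.** A reader might infer that the planned standard error is definitely too small. The article does not support that: it gives no coach ICC, and at zero the planned standard error is right. The Treatment fidelity section describes measures that narrow differences between coaches, and the content comes through a common web curriculum. This weakens the case for the upper end of the table. It does not justify assuming exactly zero, which the stated levels do.

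**The number of coaches is unknown.** A reader might also infer that there are few coaches. The only hint is the small call centre, and that remark covers all staff. With 20 coaches and ICC 0.01 the error rate is about 5.5%, which is minor. This objection stands, and is why the size is given as a range.

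**Control families also speak to a coach.** The article does not say whether the same coaches work in both arms. If they do, shared coach effects would partly cancel and the table overstates the inflation. Full cancellation is unlikely when one arm has one call and the other has weekly calls over 11 sessions.

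**Coaches may be regarded as fixed.** If the aim is to evaluate this particular trained team, and families are assigned to coaches without regard to prognosis, between-coach variance need not enter the standard error. That is a defensible target. The article neither states it nor describes how families are assigned, and the result would then not extend to other coaches.

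**The detail may sit in an analysis plan.** A condensed article can leave therapist effects to such a plan, and naming two levels does not forbid a further term or a sensitivity analysis. But here the levels of the primary model are written out rather than left open, so they can be judged as they stand.

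**Conclusion.** The point holds conditionally. The stated two-level model makes no allowance for intervention families sharing coaches, in a trial whose own text makes the coach central to delivery and pacing in one arm only. Whenever the coach ICC is above zero and coaches are treated as a sample from a wider pool, the standard error of the arm difference is too small and the test is too liberal.

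The size cannot be settled from the article. The range of about 5.5% to 13% for the true error rate rests on 175 completers per arm, clustering confined to the intervention arm, and assumed values for both the number of coaches and the ICC. Coaches shared between arms, or an ICC held near zero by training and supervision, would bring it closer to 5%. The matter is worth correcting because the remedy is cheap, but it is not a demonstrated error of known size.

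**What to change.** Record the coach for each family, including the coach who makes the single control call. Add a coach random effect for intervention families, treating each control family as its own cluster (a partially nested model), with small-sample degrees of freedom. If coaches serve both arms, let the coach effect differ by arm instead. Put this in the primary model or, at minimum, prespecify it as a sensitivity analysis. Report the number of coaches, the families per coach and the estimated coach variance.

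The cost is one extra variance component in a multilevel analysis already planned (or slightly more if the effect differs by arm), with no change to recruitment or delivery. The downside is a somewhat wider interval and, if coaches are few, an imprecise estimate of the coach variance. The latter is a fair argument for the sensitivity-analysis route.

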### Study hypotheses

#### Primary hypothesis

The primary hypothesis of this study is that the Strongest Families Smart Website intervention will reduce child disruptive behaviour symptoms and impairment scores on the *The Child Behavior Checklist-Parent Report Form (CBCL) 1½–5 years* of the Achenbach System of Empirically Based Assessment (ASEBA) [52] after treatment and at one year follow-up, compared to the Education Control condition.

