#### Sample size

As per Cohen’s [59] suggestion that standardized effect sizes of 0.20, 0.50 and 0.80 be considered as small (detectable), medium and large, respectively, we expect to observe medium to small incremental effects in the order of 0.30 to 0.35 standard units between the intervention and control groups, accounting for multiple comparisons using hierarchical linear modelling (HLM) analysis. This would require 250 participants per group for the trial, allowing for 30% attrition over time. It is expected that adding data from one year follow-up will increase the power to detect differences. An alpha of 0.05 was chosen on an *a priori* basis for the statistical analyses in order to decrease the probability of type II errors.

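### If the primary growth model is linear in time, as its wording implies, it misestimates a treatment effect that arises early and then holds or fades, and it gives no direct estimate of the after-treatment effect

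*Protocol article*

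**What the plan says.** The Statistical analyses section of the protocol article first leaves four model families open: "Latent growth analysis, mixed effects regression, structured covariance analysis, or hierarchical linear modeling (HLM) will be used". It then names growth curve analysis as primary for CBCL externalizing and says that it will "estimate parameters of growth (i.e., the slope of the outcome scores over time) for each individual, and compare these" between the arms. A second quantity comes from the same model: "net differences in response will be estimated by transposing the intercept to the end of the trial". This is presented as the formal test of outcome differences. The section mentions no curvature term, no visit factor and no 6-month contrast.

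The Primary hypothesis claims a reduction "after treatment and at one year follow-up, compared to the Education Control condition". Under Measures, "all post-screening measures are administered at baseline, at 6 months and at 12 month follow-up", so 6 months is the only visit that can stand for the after-treatment time point.

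On timing, the section on the Strongest Families components has coaches supporting parents "during the initial 11-week phase and booster sessions". It adds: "There are also two booster sessions to encourage maintenance of skills and outcome gain". The boosters fall 2–3 and 4–5 months after the intervention.

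**The concern.** A single slope over three visits is a straight line. It assumes that the arm difference grows at a constant rate from randomisation to month 12. The programme's schedule points elsewhere: the core sessions end at about 2.5 months if parents keep pace, and the boosters are meant to preserve what was gained. If the effect follows the treatment, it rises before month 6 and then holds or fades.

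A line fitted to that pattern is too low at 6 months and too high at 12. The after-treatment effect is one of the two time points in the primary hypothesis, yet neither the slope nor the moved intercept estimates it directly. The one-year difference, which carries the claim of lasting benefit, would partly reflect the 6-month result.

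**Working it through.** **Inputs from the protocol article.** Visits at 0, 6 and 12 months (Measures); effect 0.30 to 0.35 SD, 250 per group, 30% attrition, alpha 0.05 (Sample size); 1:1 allocation (Design of the study). **Assumed:** two-sided testing, 80% power, unit SD, compound-symmetric correlation 0.5 unless stated, and the effect patterns below.

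**The plan's own figure.** n = 2(1.96 + 0.8416)²/0.30² = 174.4, so 175 per arm; 175/0.70 = 250. This matches. (An effect of 0.35 at 90% power also comes close: 172, then 246.)

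**Weights of a straight line.** Code time as 0, 1, 2. With complete data and separate baselines, least squares, compound symmetry and random intercept plus slope all give:
- slope per 6-month step: (−1/2, 0, 1/2)
- fitted 6-month value: (1/3, 1/3, 1/3)
- fitted 12-month value (the moved intercept): (−1/6, 1/3, 5/6)

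**Bias.** Let the true arm differences be 0, d6 and d12, and let c = d6 − d12/2.
- 6 months: (d6 + d12)/3 − d6 = −2c/3
- 12 months: d6/3 + 5·d12/6 − d12 = +c/3

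Both vanish only when c = 0, that is, when the effect grows linearly.

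| True pattern | c | Fitted at 6 months | Fitted at 12 months |
|---|---|---|---|
| held (0, d, d) | 0.5d | 0.67d | 1.17d |
| half fade (0, d, 0.5d) | 0.75d | 0.50d | 0.75d |
| full fade (0, d, 0) | d | 0.33d | 0.33d |

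**Chance of a significant one-year result after full fade.** The sum of squared end-of-trial weights is (1 + 4 + 25)/36 = 0.833. Variance per child is 0.5 × 0.833 + 0.5 × 1² = 0.917. SE = √(0.917 × 2/175) = 0.102. The fitted difference is 0.30/3 = 0.10, so z = 0.98. The two-sided rejection probability is Φ(0.98 − 1.96) plus a negligible second tail, about 16%. The slope test has expectation zero here and rejects 5% of the time.

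**Power at d = 0.30, 175 per arm.** The slope test is the 12-month change, with SE = √(2(1 − 0.5) × 2/175) = 0.107. The baseline-adjusted 6-month contrast has SE = √((1 − 0.5²) × 2/175) = 0.0926.

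| Pattern | Slope test | End-of-trial test | Baseline-adjusted 6-month contrast |
|---|---|---|---|
| held | 80% | 93% | 90% |
| half fade | 29% | 59% | 90% |

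**Sensitivity.**
- AR(1) covariance (parameter 0.5 or 0.7) or equal baselines, complete data, held effect: 0.52d–0.60d at 6 months and 1.03d–1.10d at 12. The direction is unchanged.
- AR(1), separate baselines, full fade: the fit is linear in the pattern, so it equals twice the half-fade value minus the held value. That is 2 × 0.65 − 1.10 = 0.20d and 2 × 0.60 − 1.07 = 0.13d, below the 0.33d above.
- Weight of the 6-month visit in the 12-month slope contrast, whose complete-data weights are (−1, 0, 1): about 0.09–0.16 with 30% monotone attrition. With equal baselines it is about 0.07–0.18 on complete data and 0.16–0.28 with attrition. With equal baselines these weights are also the multiples of d fitted at 12 months under full fade.

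**The case against.** The strongest reply is that linearity is an inference. The section never calls the time trend linear, it speaks of parameters in the plural, and two of the four families it lists could hold a visit factor. A journal article may leave time coding to an analysis plan that is not shown. This stands in part, and it is why the point is conditional. But the article does more than leave time coding open: it glosses the growth parameter as the slope. With three visits, a separate quadratic for each child would leave no residual degrees of freedom, so a line is the practical reading.

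Second, the documents show front-loaded treatment, not a front-loaded effect. The second booster falls at about 6.5–7.5 months if parents are on pace, and parents may take longer over sessions. This also stands: every magnitude above is a scenario.

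Four stronger readings are tempting, and the documents do not support them.
- A reader might infer that the 6-month visit is ignored. Its weight in the slope test is exactly zero only with complete data and separate baselines, and it has weight 1/3 in the end-of-trial test.
- A reader might infer that a short-lived effect would be reported as a one-year effect. In the full-fade scenario that happens about 16% of the time, and less under the other covariances.
- A reader might infer that the Sample size statement, "It is expected that adding data from one year follow-up will increase the power to detect differences", is wrong. It is not about the slope test. In the held case the end-of-trial test has 93% power, against 80% for a 6-month change score, although part of that gain is the 1.17d overshoot.
- A reader might blame the 29% slope power on the model. It needs the effect to halve, and much of the loss is then simply the smaller 12-month effect of 0.15 SD.

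**Conclusion.** The concern holds conditionally. If time enters linearly, as the wording implies, the primary model estimates the 6- and 12-month differences without bias only when the effect grows in a straight line. For a held effect, the 6-month difference is a third too low and the 12-month difference a sixth too high, given complete data and separate baselines. An equal-baseline or AR(1) model reduces the 12-month error but not its direction. The slope comparison rests almost wholly on baseline and month 12, and the after-treatment effect has no direct estimate.

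The validity of the test of no effect is not in question: with no difference at any visit, type I error is nominal. A held effect of 0.30 SD keeps about 80% slope power if baseline and 12-month scores correlate at 0.5. The defect lies in what is estimated and how a one-year difference would be read. It merits correction, but it does not make the trial unable to answer its question.

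**What to change.** Make the primary analysis a repeated-measures mixed model with visit as a three-level factor, arm-by-visit terms, unstructured within-child covariance and a common baseline mean. Report separate arm differences at 6 and 12 months, and state how the two together bear on the primary hypothesis. Keep the linear growth curve as a secondary description of trajectories. The sentence on power in the Sample size section can stay.

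This estimates d at both visits when the effect is held, and it remains unbiased by effect shape if the effect grows or fades. No new data are needed. The mean model has five parameters with a common baseline (six without) against four for two lines, and the unstructured covariance has six against four for random intercept, slope and residual.

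If the effect truly grows linearly, a little precision is lost. At correlation 0.5, a common-baseline line has 12-month weights (−0.545, 0.182, 0.909), so its variance per child is 0.5 × (0.297 + 0.033 + 0.826) + 0.5 × 0.546² = 0.727 and its SE is √(0.727 × 2/175) = 0.0912. The visit-specific contrast has 0.0926. The change should be settled before any unblinded analysis.
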